## **6. SAFETY**

### **6.1 ADVERSE EVENT REPORTING**

In this study an adverse event is defined as any untoward medical occurrence in a participant which may or may not have a causal relationship with the study treatment. An adverse event can therefore be any unfavorable or unintended sign, symptom or condition and/or an observation that may or may not be related to the study treatment. A register of adverse events will be kept and will be reviewed by the research team fortnightly.

### **6.2 SERIOUS ADVERSE EVENT REPORTING**

In this study a serious adverse event is defined as any untoward medical occurrence that results in the following: death, is life-threatening, requires inpatient hospitalisation, persistent or significant disability/incapacity, or a condition requiring medical or surgical intervention, such as cardiac arrest, acute pulmonary oedema, cardiac arrhythmias, epileptic seizure. A register of serious adverse events will be kept and reviewed by the research team fortnightly.

### **6.3 DATA SAFETY AND MONITORING BOARD**

A data safety and monitoring board (DSMB) will comprise two independent and registered emergency medicine clinicians, employed within a major hospital health service in Melbourne, Victoria. Both are emergency medicine consultants.

The DSMB will receive a fortnightly update of study enrollments that will include any adverse events. All major adverse events (cardiac arrest, acute pulmonary oedema, cardiac arrhythmias, epileptic seizure) will be reported within 24 hours to the DSMB. (Please see note in “Blinding and Unblinding” regarding coding of the treatment arms).

### **6.4 EARLY TERMINATION**

The DSMB may advise the trial be prematurely discontinued if concern arises about adverse event rates or delayed response rates.

## **7. BLINDING AND UNBLINDING**

Blinding will occur in the following way: study packs will be prepared by Pharmpackpro Pty Ltd. Two vials will be in the study packs, one containing the active Naloxone and one containing placebo. Vials will be individually and clearly labeled either ‘intramuscular’ or ‘intranasal’. During the course of the trial only Pharmpackpro Pty Ltd will know which packs contain either active Naloxone preparation or placebo, or intramuscular preparation or placebo.

Pharmpackpro Pty Ltd will provide the research co-ordinator with a code assigned to each treatment arm but that does not reveal whether the arm contains the active Naloxone or placebo. In this way, the two treatment arms will be distinguishable for fortnightly analysis, but the researchers will remain blinded. The packs will be

sequentially numbered, and coded according to treatment arm, and the pack number and code used during the trial will be recorded, along with the other clinical observations by the MSIC staff on the data-form. In this way, the participants, the nurses administering the Naloxone and the researchers will be blinded to the two treatment arms.

Unblinding will occur in the following way: once all participants have been recruited, and the active phase of the trial has concluded, clinically-significant differences in the responses of the participants will be analysed. After this analysis, treatment allocations will be de-coded by obtaining from Pharmpackpro Pty Ltd. the numbers of the packs and codes that correspond to the two treatment arms, thereby revealing to which treatment arm each of the participants belongs.

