# **Randomised, double-blind clinical trial comparing IN and IM Naloxone for suspected opioid overdose**

## **1. BACKGROUND**

### **1.1 DISEASE BACKGROUND**

Drug overdose is a leading cause of death among people who inject drugs. The Sydney Medically Supervised Injecting Clinic (MSIC) was established in 2001 with the primary aim of reducing the morbidity and mortality of drug overdoses in the local area. Within the first nine years of opening, the MSIC had treated over 3000 acute opioid overdoses on site without a single fatality. Overdose management protocols are in place for nursing staff to administer intramuscular Naloxone, as well as provide external airways resuscitation and oxygen, for clients who overdose within the MSIC. Due to the high frequency of opioid overdose routinely treated onsite, and the experienced staff who manage them, the MSIC provided a unique and ideal setting to investigate alternative Naloxone administration routes.

IM and intravenous Naloxone are currently the standard modes of emergency treatment for an opioid overdose, however pharmacology data indicate that Naloxone is 100% bioavailable through the nasal mucosa. Naloxone can be sprayed into the nose via a mucosal atomisation device and evidence indicates that IN Naloxone may not only be as effective a route of administration as IM administration, but also a practical and realistic alternative. There have been a number of previous studies examining IN Naloxone. These have generally been cohort studies with only two previous randomised trials neither of which were double-blinded.

The first randomised trial used a large volume of fluid for intranasal administration which may have limited efficacy. The subsequent trial showed a slightly higher rate of 'rescue' Naloxone given to those patients whose initial dose was delivered intranasally. The authors felt that this may have been due to the non blinded nature of the study, with the additional dose being a subjective decision dependent of individual paramedic's comfort in waiting for a response.

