## Statistical analysis Plan - final

Analyses will be conducted in accordance with the International Conference on Harmonization E9 statistical principles [Lewis, 1999], and reported according to the CONSORT recommendations [Moher et al, 2001; Hopewell et al, 2008]. An intention-to-treat analysis will be performed for all participants who were randomized to receive either mode of treatment (IN and IM administration).

Descriptive analyses will be conducted to compare trial arms (IN and IM) for observed differences in demographics and other important clients' characteristics.

As the trial progressed it was noted that there were several individuals who experienced multiple overdoses who were randomized into the study, introducing clustering. Therefore the main analysis for comparing the incidence rate of secondary naloxone administration mode (IN and IM) will be performed using Generalized Linear Mixed Effects (GLMM) analysis [McCulloch, 2001] for a binary outcome variable with a logistic link function to account for within-client clustering effects because of the multiple overdoses. A Generalized Estimating Equation (GEE) technique with unstructured covariance pattern will be implemented for this purpose. Odds ratio (OR) and 95% confidence interval (CI) will be reported as intervention impact, as per the original analysis plan.

For secondary time to event outcomes medians and 95% CIs at each study arm and Kaplan-Meier survival plots will be reported as descriptive measures. Cox proportional hazards regression models, with shared Gamma frailties to account for within-client clustering effects, will be used to compare between group hazard rates. Hazard ratio (HR) and 95% CI will be reported as intervention impact as per the original analysis plant. We will explore the proportional hazards assumption through visual inspection of survival and hazard plots.

In order to fully explore the effects of repeat presentations, secondary analyses involving only the first overdose of clients will be conducted using analogous methods for primary binary (logistic regression) and secondary time to event (Cox proportional hazards) outcomes. All analyses will be carried out using Stata (version 15; Stata, College Station, TX).

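### A fixed arm code on every pack, recorded by site staff, leaves the blinding of nurses and researchers open to inference

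*Supplement*

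**What the plan says.** Final protocol, section 7 (Blinding and Unblinding): the person coordinating the research is supplied by the packaging company "with a code assigned to each treatment arm but that does not reveal whether the arm contains the active Naloxone or placebo". The section adds that "the two treatment arms will be distinguishable for fortnightly analysis, but the researchers will remain blinded". The packs themselves will be "sequentially numbered, and coded according to treatment arm, and the pack number and code used during the trial will be recorded", next to the other clinical "observations by the MSIC staff on the data-form". From this it concludes that "the participants, the nurses administering the Naloxone and the researchers will be blinded to the two treatment arms".

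Section 5.7 describes the double-dummy packs, two attending staff and a third who charts vital signs. It makes a client eligible for a second, open intramuscular dose if the response is inadequate at ten minutes. The final SAP takes the occurrence of that second dose as its main binary outcome. Section 1.1 reports that the authors of the earlier unblinded trial, on finding more rescue doses after intranasal treatment, felt that "this may have been due to the non blinded nature of the study, with the additional dose being a subjective decision".

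**The concern.** A double-dummy pack hides the route in that one pack. An arm-level code links all packs to each other. With two fixed codes, a belief formed about one code carries over to every past and future pack that shows it. With a unique pack number alone, a guess about one pack says nothing about the next. The conclusion in section 7 that nurses and researchers are blinded therefore does not follow from the arrangement it describes.

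At stake is the main outcome. Whether a client gets a second dose depends on a judgement made at the bedside, and section 1.1 gives possible bias in that decision as a reason to interpret the earlier trial with care. If the code can be read before a pack is used, allocation concealment is weakened too, because entry depends on a judgement that the initial response to oxygenation was inadequate. Analysis cannot afterwards remove bias that entered through the decision to re-dose.

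**Working it through.** The plan gives no figure on this point, so there is none to reproduce. The check has two parts.

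**1. Reading the text**

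- Number of codes: one per arm, so two (section 7).
- Where the code appears: packs are coded by arm, and site staff write the code down for each case (section 7).
- Who else holds it: the research co-ordinator, so that the arms can be compared fortnightly (section 7).
- Masking or rotation of the code: none is described in the final protocol or the SAP.
- Need for the code at the site: none is apparent. Packs already carry sequential numbers, and the de-coding step in section 7 obtains pack numbers from the packaging company.
- Need for it in monitoring: final section 6.3 lists only enrolments and adverse events in the fortnightly update, with a cross-reference to the coding in section 7. Section 6.4 lets the DSMB act on adverse event rates or delayed response. By-arm monitoring can be served without a code at the bedside.

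**2. How informative a tally by code would be**

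Inputs: planning rates of 18% intranasal and 4% intramuscular (section 8); 1:1 allocation, implied by 99 per group (section 8). The other pairs of rates below are assumptions, chosen to show the range.

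*A single rescue.* With equal allocation, the probability that a code under which one rescue was seen is the intranasal code is 0.18 / (0.18 + 0.04) = 0.82.

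*A full tally.* Let X ~ Bin(n, p_IN) and Y ~ Bin(n, p_IM) be the rescues under the two codes after n cases per arm. The probability that the intranasal code is strictly ahead is

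P(X > Y) = Σₓ P(X = x) · P(Y ≤ x − 1).

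At the planning rates:

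| n per arm | P(X > Y) |
|---|---|
| 25 | 0.925 |
| 40 | 0.974 |
| 50 | 0.986 |

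At n = 25 per arm, for different true rates:

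| p_IN vs p_IM | P(X > Y) | Source of rates |
|---|---|---|
| 18% vs 4% | 0.925 | section 8 |
| 12% vs 4% | 0.79 | assumed |
| 10% vs 5% | 0.66 | assumed |
| 10% vs 10% | 0.405 | assumed |

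In the last row each code is ahead with probability 0.405 and they tie with probability 1 − 2 × 0.405 = 0.19, so the tally carries no information about which code is which. One code would still be ahead in 2 × 0.405 = 81% of such tallies. A mistaken belief could therefore form and steer decisions by code.

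**The case against.** The case on the other side has several parts, and most of it limits the point without removing it.

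- **Who sees the code.** A reader might infer that the nurses who decide on the second dose will know the allocations. The documents do not support that. Section 7 says only that site staff record the code. It does not say who completes that field, where on the pack the code is printed, or whether the person judging response at ten minutes has seen it. This stands. Exposure of the treating team is a natural reading of section 7 alongside the staffing in section 5.7, but it remains an inference.
- **The tally.** The probabilities assume that every case is counted by code. Under section 9, data-forms are locked away for the research team and the database is open only to investigators. A nurse would have memory and conversation to go on. This stands: the figures fit someone holding all by-code data, such as the research co-ordinator, and are an upper-end illustration for bedside staff.
- **The gap.** The 18% vs 4% figures come from a trial whose authors thought that lack of blinding might explain the difference. If the routes are equally effective, the counts do not identify the code. This stands, and is why a range is shown.
- **Existing safeguards.** Packs are double-dummy, the code does not name the active route, consent is sought before the overdose, enrolment is consecutive, and section 5.7 ties naloxone to existing clinical criteria. These narrow the scope for bias and for selecting cases by the next code. They do not undo the link that a constant code creates between packs.

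It is also tempting to say that differences in response time would reveal the code sooner than rescue counts. The documents give no expected response times by arm, so this cannot be assessed. Nor does section 1.1 establish that subjectivity caused the earlier result; it reports a conjecture by that trial's authors.

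**Conclusion.** The point holds as a conditional weakness in the blinding. One of two constant arm codes is put on each pack, recorded at the site, and held by the research co-ordinator for by-arm review during recruitment, and no text in the final protocol or SAP masks it. A belief about one code, right or wrong, extends to all of roughly 200 allocations. For a person with a complete tally at 25 cases per arm, the chance that the intranasal code is strictly ahead runs from 0.925 at the planning rates down to 0.66 at an assumed 10% vs 5%; at equal rates the tally is uninformative. These figures assume 1:1 allocation and independent cases, although the SAP notes that some clients enter more than once.

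The documents do not show that the code was broken, that the deciding nurse is the person who records it, or that any result was biased. The blinding that section 7 claims is not secured by the procedure it sets out.

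**What to change.** Amend section 7 so that packs show only a unique pack number that carries no information about the arm, and the data-form records only that number. Keep the pack-to-arm list with the packaging company. During the trial, release it only to a person outside the treating and research teams who prepares a closed report for the DSMB. The site research team does no by-arm analysis, coded or not, before recruitment ends. De-coding at the end proceeds by pack number, as section 7 already provides.

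The cost is a change of protocol wording, relabelling of unused packs, a revised data-form field, and a small merge of pack numbers with arms outside the site team for each DSMB report. The research team also gives up its own by-arm view during the trial.

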## 8 STATISTICAL CONSIDERATIONS

Recently, the study findings of a RCT comparing IN and IM Naloxone have been reported. In that study, requirement for a secondary dose of Naloxone was reported as IN:18% vs IM:4%. We estimate (using JavaStat) that we would need a sample size of 99 per group to achieve adequate power (power=0.8, with 95% confidence) to detect a difference of 14% in requirement for secondary Naloxone.

Descriptive analyses (proportion, median, effect size difference with 95% confidence intervals) will be conducted to compare demographic characteristics and over-dose related variables for the two groups by allocation (IN and IM) (e.g., age, gender demographic data, prior drug use, previous alcohol use, etc).

Primary outcomes will be compared by univariate analysis including odds ratio with 95% CI, hazard ratio (HR) and chi-square analysis. Response time will be compared using a Kaplan-Meier survival curve. A clinically significant difference in response time will be defined as two minutes.

For cases in which response times are not recorded on patient recovery, and subsequent discharge from the treatment room, a default figure of 10 minutes will be recorded.

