### 3.2 NUMBER OF PARTICIPANTS

- Approximately 200

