#### 5.4 RECRUITMENT AND SCREENING

- Recruitment: all MSIC clients are potential participants for this study, as all MSIC clients may potentially experience opioid overdose while using the centre. Flyers will be placed around MSIC notifying clients of the study.
- Screening: All clients with symptoms/signs of an opioid overdose requiring Naloxone administration will be eligible for the study. This is based on existing and approved MSIC protocols and clinical criteria for overdose include:
  - glasgow coma score < 13
  - pinpoint pupils
  - respirations < 10/min and/or
  - reduced oxygen saturations (< 95%).

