## 5.7 RANDOMISATION PROCEDURE

MSIC staff will manage drug overdoses using existing clinical protocols. These state that a client will receive airway management and oxygenation either via a Hudson mask or artificial ventilation (bagging) for five minutes before being assessed as to the need for Naloxone. Where a client's response after five minutes is inadequate, Naloxone will be administered by a registered nurse in accordance with existing standing orders from the Medical Director.

Study participants will receive a random allocation of Naloxone in one of 2 forms:

- Active intranasal Naloxone and intramuscular placebo, or
- Intranasal placebo and active intramuscular Naloxone.

Study packs will be pre-prepared and contain two clearly labelled vials – 1) Intranasal - Naloxone 800mcg/1mL or placebo (1mL) for IN administration and 2) Intramuscular - 800mcg/1ml or placebo for IM administration. The vials will be labelled as intranasal and intramuscular, therefore the person administering the drugs will be blinded to the treatment arms. As per MSIC protocol, two staff members will attend the patient during treatment of opioid overdose. A third attending staff member will record the participants' vital signs on a chart. The chart is currently in use for overdoses.

To minimise potential bias, the order in which the drug will be administered will be rotated approximately midway through the study. Initially the intranasal drug preparation will be administered first, followed by the intramuscular drug preparation. Approximately midway through recruitment (e.g., after 100 enrolments), the intramuscular drug preparation will be administered first, followed by the intranasal drug preparation.

Contents of the vial for IN administration will be drawn into one syringe. Staff will attach the syringe to a MAD, and administer 0.5mL (400mcg) into each nostril, depressing the syringe rapidly to achieve adequate atomisation. In this way, each study participants will receive 0.5mL of fluid in each nostril. Supportive care/oxygenation will be administered simultaneously, in accordance with existing MSIC clinical protocols

Administration of the IM injection will be by standard practice of drawing the full 1ml into a single 5ml syringe and administering to the deltoid muscle via a 23g needle.

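### No planned model adjusts for overdose severity before dosing; if severity is prognostic this gives up power, mainly in the secondary response-time analysis

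*Supplement*

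**What the plan says.** **Comparison of arms.** Section 8 of the final protocol reads "Primary outcomes will be compared by univariate analysis including odds ratio with 95% CI, hazard ratio (HR) and chi-square analysis". It names no covariate.

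**SAP.** The main analysis of the second naloxone dose is a logistic model (GLMM, implemented by GEE) that allows for several overdoses per client. The time-to-event outcomes, which the SAP classes as secondary, are compared with "Cox proportional hazards regression models, with shared Gamma frailties to account for within-client clustering effects". The first-overdose analyses use analogous methods. Baseline characteristics serve only to describe the arms.

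**What is known before dosing.** Section 5.4 of the final protocol lists the clinical criteria for overdose, among them "glasgow coma score < 13", pinpoint pupils, respirations under 10 per minute and oxygen saturation under 95%. Under section 5.7, need for naloxone is judged after five minutes of airway care, and "A third attending staff member will record" vital signs on the overdose chart. Section 7 says clinical observations go on the data-form with the pack number and code.

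**Planned size.** Section 8 plans for "adequate power (power=0.8, with 95% confidence) to detect a difference of 14% in requirement for secondary Naloxone" and says "we would need a sample size of 99 per group".

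**The concern.** A second dose is given to clients who have not responded adequately at ten minutes. Consciousness and breathing just before the first dose are therefore plausible predictors both of that outcome and of response time. The and/or wording of the entry criteria also lets in overdoses of differing depth.

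In a Cox or logistic model, leaving out a prognostic baseline variable has two effects even when randomisation is perfect:
- The test of treatment loses power.
- The unadjusted hazard or odds ratio lies nearer 1 than the ratio at a given severity.

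The stated aim is to learn whether the intranasal route is as effective as the intramuscular one. In that setting, a low-powered comparison that finds no difference says little. What is at stake is efficiency, and having a severity adjustment fixed before the allocation is known.

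**Working it through.** **1. The plan's own figure.** Inputs (section 8): 18% vs 4%, power 0.80, 95% confidence, taken as two-sided 0.05. The mean proportion is 0.11.

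n = [1.96·√(2·0.11·0.89) + 0.8416·√(0.18·0.82 + 0.04·0.96)]² / 0.14² = 77.2, so 78 per group.

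With continuity correction: (77.22/4)·[1 + √(1 + 4/(77.22·0.14))]² = 90.9, so 91.

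The stated 99 is not reproduced, but it errs on the large side and does not bear on this point. At 99 per group, power is Φ[(0.14·√99 − 1.96·√0.1958)/√0.186] ≈ 0.89. Expected second doses: 99·0.18 + 99·0.04 = 21.8, about 22.

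**2. Second dose, with and without severity.** Simulation with 99 per arm, marginal risks held at 18% and 4%, one standardised severity score, likelihood-ratio test, 4,000 trials per row. The log odds ratio per SD is assumed.

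| Log OR per SD | Power, unadjusted | Power, adjusted | Gain (points) |
|---|---|---|---|
| 0 | 92.0% | 92.2% | 0.2 |
| 0.5 | 90.9% | 91.6% | 0.7 |
| 1.0 | 90.9% | 93.8% | 2.9 |
| 1.5 | 92.2% | 96.1% | 3.9 |

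**3. Response time.** The protocol gives a two-minute relevant difference but no hazard ratio, median or event count. Assumed here: conditional HR 0.65, baseline hazard 0.25 per minute, censoring at 10 minutes, 198 independent overdoses, 2,000 trials per row.

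| Log HR per SD | Share responding | Large-sample unadjusted HR | Power, unadjusted | Power, adjusted | Gain (points) |
|---|---|---|---|---|---|
| 0 | 0.84 | 0.65 | 80% | 80% | 0 |
| 0.5 | 0.82 | 0.69 | 67% | 79% | 12 |
| 1.0 | 0.78 | 0.74 | 46% | 76% | 30 |
| 1.5 | 0.76 | 0.78 | 30% | 73% | 43 |

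Hand check: power ≈ Φ(½·√d·|log HR| − 1.96), where d is the number of responses. In the 0.5 row, d = 0.82·198 = 162 and ½·√162 = 6.37. Unadjusted (HR 0.694): Φ(6.37·0.365 − 1.96) = 0.64. Adjusted (HR 0.65): Φ(6.37·0.431 − 1.96) = 0.78. Both are close to the simulated values.

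**4. A different baseline hazard.** Weibull shape 1.5, about 133 responses, 1,500 trials per setting, conditional HR again 0.65. A second run of the same set-up gave:
- Log HR 0.2: power 0.69 vs 0.70, unadjusted HR 0.65.
- Log HR 0.4: power 0.64 vs 0.71 (first run 0.63 vs 0.68), unadjusted HR 0.66.
- Log HR 0.7: power 0.53 vs 0.69 (first run 0.53 vs 0.68), unadjusted HR 0.70.

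**5. Does the planned frailty supply the adjustment?** Simulated with 198 overdoses, 75% as many clients (assumed) and 120 trials per case. Median HR without and with shared gamma frailty:
- Log HR 0.5: 0.67 and 0.66.
- Log HR 1.0, severity varying only from one overdose to the next: 0.74 and 0.74.
- Log HR 1.0, half the severity variance between clients: 0.73 and 0.69.

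The frailty belongs to the client and severity to the overdose, so recovery is partial at best. The first-overdose analyses have one record per client, so a shared frailty has no repeat overdoses there from which to recover it.

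**The case against.** An unadjusted primary analysis is an accepted choice, and much of the case for leaving it alone is sound.

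- **The powered endpoint barely gains.** The second dose is the main analysis, its power already exceeds the planned 0.80, and adjustment adds at most about 4 points. This stands. A reader might infer that the primary comparison is materially underpowered for want of covariates, and the figures do not support that.
- **The pull toward 1 is not bias.** A reader might infer that the unadjusted analysis is wrong, or tilted toward finding the routes alike. It is not. It is a valid randomised comparison of a marginal effect, and a GEE targets a population-averaged odds ratio by design. The gap from the severity-conditional ratio is non-collapsibility, not confounding. In the Weibull rerun the standard error of the log hazard ratio did not fall with adjustment (0.175 vs 0.177). The power comes from a larger conditional effect, not a narrower interval.
- **Prognostic strength is not shown.** Cases enter after inadequate response to five minutes of care and against set thresholds, which may narrow the range of severity. At log HR 0.2 the loss is about one point. This stands, and is why a range is given.
- **Data and fitting.** The data form is not shown, so it is an inference that a numeric pre-dose score is kept. Respiratory rate may be hard to interpret in a client who is being bagged. With about 22 events, treatment plus two covariates leaves 22/3 ≈ 7 events per parameter. Dropping overdoses with missing baseline values would conflict with the SAP's intention-to-treat statement. These points shape the fix.

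What survives is the power loss for response time. It appears under both baseline hazards, and the client frailty does not reliably remove it.

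**Conclusion.** The concern holds as a matter of efficiency. Neither current document adjusts any comparison for severity, although severity is assessed before dosing.

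- **Response time (secondary in the SAP):** about 5 to 12 power points lost at a log HR of 0.4 to 0.5 per SD, more if severity is a stronger predictor, none if it is not prognostic. These figures assume a conditional HR of 0.65, follow-up to 10 minutes and independent overdoses.
- **Estimate:** at the same strengths the unadjusted HR is about 0.66 to 0.69 against a conditional 0.65. Larger gaps need stronger prognosis.
- **Second dose:** about 0 to 4 points.

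The change is worth making because it is cheap and should be settled before the arms are known. The validity of the planned comparison is not in doubt.

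**What to change.** Before de-coding, add to the SAP:

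1. **Cox models.** Include the last pre-naloxone Glasgow Coma Score and respiratory rate as fixed continuous covariates in the frailty Cox model and its first-overdose counterpart. Report the unadjusted hazard ratio beside the adjusted one.
2. **Data source.** The sponsor should confirm that both values are on the chart or data-form and state which reading counts, including for clients receiving artificial ventilation.
3. **Missing baseline values.** Fill them by a simple rule blind to arm, such as the overall mean, so that every randomised overdose stays in the analysis.
4. **Logistic model.** If it is adjusted, use at most these two terms and show the unadjusted odds ratio alongside.

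The cost is a short SAP paragraph, with no new data collection if the values are confirmed. The drawbacks are that adjusted estimates are conditional on severity, so they answer a slightly different question from the unadjusted ones, and that the binary model has few events per parameter.

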Any client who fails to respond adequately after ten minutes will be eligible for a second dose. This dose will be a known dose of 800mcg of Naloxone administered intramuscularly and not subject to randomisation. In this manner, all overdoses will receive the same clinical care they would have otherwise, under existing approved clinical protocols, with Naloxone administered at the same time point, in response to the same clinical criteria. The only exception will be that the need for any additional dose of Naloxone will be assessed at ten minutes post- first dose as opposed to five minutes. Importantly, all clients will be adequately oxygenated and fully monitored during this time.

Post analysis, the treatment allocations will be de-coded.

The preparation of Naloxone and placebo will be manufactured by a registered pharmaceutical company, Sypharma Pty Ltd, and will comply with national medication quality and safety standards. The complete study packs will be packed by Pharmpackpro Pty Ltd.

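### Unrecorded response times are set to a fixed 10 minutes of unstated event status, which distorts the response-time medians and hazard ratio

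*Supplement*

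**What the plan says.** Final protocol, section 8: where "response times are not recorded on patient recovery, and subsequent discharge from the treatment room, a default figure of 10 minutes will be recorded". The rule is worded for clients who recovered and left the treatment room. It gives no event or censoring status.

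Final protocol, section 5.7: "Any client who fails to respond adequately after ten minutes will be eligible for a second dose", with the need for that dose "assessed at ten minutes post- first dose as opposed to five minutes".

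Response time is then analysed in both documents. In protocol section 8, "Response time will be compared using a Kaplan-Meier survival curve", a hazard ratio is listed among the comparisons, and two minutes is the clinically significant difference. In the SAP, "For secondary time to event outcomes medians and 95% CIs at each study arm and Kaplan-Meier survival plots will be reported", and "Cox proportional hazards regression models, with shared Gamma frailties to account for within-client clustering effects, will be used to compare between group hazard rates".

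The SAP does not mention the default. Neither document plans a count of defaulted times by arm, a sensitivity analysis, or a rule for how rescued clients enter the time analysis.

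**The concern.** The default is single-value imputation of an unknown time, analysed as though it had been observed. The value sits at one end of what is possible. A recovered client who needed no second dose would normally have responded before the 10-minute assessment, so the rule places that client among the slowest responders. If the rule also reaches rescued clients, who had not responded adequately at 10 minutes, the value is too early for them.

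At stake is the comparison of response times: the Kaplan-Meier medians, the hazard ratio and the judgement against the two-minute threshold. The trial asks whether IN is as effective as IM, so a hazard ratio pulled toward 1 could hide a real difference in speed. Unequal recording between arms could create a difference where none exists.

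**Working it through.** The plan has no figure of its own to reproduce here. It gives no expected response times and no rate of unrecorded times. The 99 per group concerns secondary naloxone and plays no part.

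**Inputs from the documents.** Default 10 minutes; second-dose assessment at 10 minutes; threshold 2 minutes; planning rates of secondary naloxone 18% (IN) and 4% (IM).

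**Assumptions.** Response time runs from the first dose. Clients unresponsive at 10 minutes are censored there. The default applies only to clients who responded by then. The share m of those left unrecorded is varied. Cox models use Efron ties and no frailty term.

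**1. Medians, by formula.** Putting a share m of responders at 10 minutes leaves (1 − m)F(t) recorded as responding by t. The Kaplan-Meier median then solves F(t) = 0.5/(1 − m). For Weibull times with shape k and true median M:

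t = M × [−ln(1 − 0.5/(1 − m)) / ln 2]^(1/k)

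This holds under event or censored coding while the median stays below 10 minutes. Take k = 1.2 and medians of 3 (IM) and 5 (IN), so the true hazard ratio is (3/5)^1.2 = 0.54.

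- m = 10%: 0.5/0.9 = 0.556; −ln(0.444)/0.693 = 1.170; 1.170^(1/1.2) = 1.140. Medians 3.42 and 5.70, difference 2.28.
- m = 20%: bracket 1.415, multiplier 1.335. Medians 4.01 and 6.68, difference 2.67.
- m = 30%: bracket 1.807, multiplier 1.638. Medians 4.91 and 8.19, difference 3.28.

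**2. Hazard ratios, by simulation** (same set-up, 99 per arm, 1,000 trials):

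| Unrecorded, each arm | HR, coded event | HR, coded censored | Median difference (step 1), min |
|---|---|---|---|
| 0% | 0.54 | 0.54 | 2.00 |
| 10% | 0.57–0.58 | 0.61 | 2.28 |
| 20% | 0.60 | 0.66 | 2.67 |
| 30% | 0.62 | 0.70 | 3.28 |

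(The 10% event entry spans two runs.) The rejection rate falls from 0.98 with full data to 0.90 (event) or 0.49 (censored) at 30%.

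**3. Exponential times tied to the planning rates.** The rates are −ln(0.04)/10 = 0.322 for IM and −ln(0.18)/10 = 0.171 for IN. The true hazard ratio is 0.533, with medians 2.15 and 4.04, a difference of 1.89 minutes. At m = 5% the formula gives 1.89 × 1.078 = 2.04 minutes, already past the two-minute threshold. In simulation (100 per arm, 300 trials), 5%, 10%, 20% and 30% unrecorded gave:

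- HR coded as event: 0.555, 0.578, 0.598, 0.625
- HR coded as censored: 0.578, 0.617, 0.660, 0.707
- Median difference: 2.03, 2.15, 2.71, 3.27 minutes (event coding)

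**4. No true difference.**

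- Equal recording: HR about 1.0 and rejection near 5%, so no bias.
- 10% (IM) versus 20% (IN) unrecorded, Weibull, both medians 4, coded as events: HR 0.89, 12% false positives.
- 10% versus 30%: HR 0.79, 34% false positives. The spurious median difference is 4 × 1.638 − 4 × 1.140 = 1.99 minutes by formula and 2.1 in simulation. If clients unresponsive at 10 minutes are also recoded as events, the figures are 0.78 and 38%.
- Imbalance the other way (IN 5%, IM 15%, exponential): HR 1.15 with 15% false positives as events, 1.26 with 30% as censored.

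**5. Simply dropping unrecorded times** in the setting of step 3 gave HR 0.52–0.53 at 5–10% and 0.49–0.50 at 20–30%. That is closer to the truth, but now errs away from 1, because only responders can have an unrecorded time.

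**The case against.** Several points on the other side stand.

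- The main SAP analysis, the odds ratio for secondary naloxone, does not use response time. The SAP calls the time-to-event outcomes secondary, although protocol section 8 lists the hazard ratio under its primary outcomes.
- A reader might infer that the rule invents events. The wording does not support that: these clients recovered, so the response is real and only its time is assigned. Nor does the text say the value is coded as an event.
- A reader might infer that the rule tilts the result toward IN being as effective. The hazard ratio does move toward 1 under equal recording, but the median gap widens, which points the other way. The two reported summaries can therefore disagree.
- Whether the rule reaches rescued clients is unclear. Likewise, a client slow at 10 minutes is only eligible for a second dose, so a few non-rescued clients may truly have responded later.
- The double-dummy blinding makes gross imbalance in recording less likely, and nothing in the documents shows a threefold imbalance.

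Blinding does not settle the matter. It leaves the attenuation under equal recording as it is. If fast responders more often leave without a recorded time, missingness follows speed and so can differ by arm. With 30% unrecorded for responses under 2 minutes and 5% otherwise, the same rule in both arms gave 13% (IM) versus 9% (IN) of clients unrecorded, and HR 0.60 instead of 0.54. That mechanism is an assumption.

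**Conclusion.** The rule is wrong as written and should be fixed, as a matter affecting a secondary outcome. Whenever some responders lack a recorded time, a constant placed at the second-dose assessment lengthens the medians. If the routes truly differ in speed, it also distorts the hazard ratio.

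Under the stated assumptions, with 10–30% unrecorded equally, a hazard ratio of 0.54 becomes about 0.58–0.62 (event) or 0.61–0.70 (censored), and a 2-minute median gap becomes about 2.3–3.3 minutes. A true gap just under the protocol's threshold can therefore be reported as just over it. The protocol does not say to which summary that threshold applies. Without a true difference, harm arises only from unequal recording.

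The size and direction in this trial cannot be fixed from the documents, because the missing rate, its balance between arms and the coding are all unstated.

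**What to change.** Delete the 10-minute default and put the replacement in the SAP:

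- For a recovered client who was not rescued, treat an unrecorded time as interval-censored. The lower bound is the first dose, or the last charted non-response. The upper bound is the first charted response, or the 10-minute assessment if no response time is charted. Multiple imputation within the same bounds is an alternative.
- State how rescued clients enter the time analysis, and do not assign any of them a response time at or before rescue.
- State the event or censoring status of every category of client.
- Report the number of unrecorded times by arm.
- Run two sensitivity analyses, with all unrecorded times at their early bound and at their late bound.

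The cost is SAP and protocol wording, modest programming and slightly wider intervals. No new data are needed for the widest bounds, first dose to the 10-minute assessment. Whether the vital-signs chart can narrow them cannot be judged here, since the data form is not shown and no charting interval is given.
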